### Protocol modifications

Substantial modifications to the protocol require a formal amendment that has to be approved by the lead Ethics Committee. Furthermore, the changes must be re-appraised by the co-ordinating investigators and, if applicable, in agreement with the biometrician and/or DSMB. Protocol amendments will be communicated by newsletters and at trial meetings but also with each trial site individually by Data Management after the local Ethics Committee has approved it. The Investigator Site File will be updated and all relevant changes to recruitment, clinical procedures and data entry will be discussed.

### Sample size and statistical analysis

We followed statistical guidelines, recommending that clinical and statistical considerations be taken into account along with historical data when choosing a margin of non-inferiority [30]. Moreover, we note that the European Medicals Agency (EMA) and the Food and Drug Administration (FDA) often find proposed margins too lax and chose a stricter margin than the 15 and 10 percentage points used in two RCTs with non-inferiority designs for ventilation failure [5, 18, 24]. The point estimate from historical data for absolute risk reduction in intubation proportions due to NIV was found to be 20.7 and 11.9 with lower 95% confidence limits of 2.0 and 1.6 percentage points, respectively [5, 7, 8]. Taken all this into consideration, we chose Δ = 8 percentage points for our non-inferiority margin. The cited trials by Plant et al. and Carrera et al. found need for intubation in 13.5% and 15.1% of the NIV groups. We use this as a proxy for our endpoint and assuming that treatment failure is 15% in both arms, implying that 680 patients need to be analysed to have 80% power for having the upper end of the 95% CI within the margin of non-inferiority (continuity corrected *Z*-test with pooled variance) [31]. Taking into account a small drop-out rate of about 5%, we intend to recruit 720 patients in total.

The full analysis set (FAS, based on the intention-to-treat (ITT) strategy) is defined to comprise all randomized patients with AECOPD and started on ventilatory support. If, for example, pneumonia is detected within 48 h (nosocomial), such patients will not be included in the final analysis, since the initial AECOPD diagnosis is found to be erroneous. Patients who test positive for SARS-CoV-2 within 48 h will not be included in the full analysis set. For the confirmatory analysis, linear regression with the stratification variables and the arm as covariates will be used and where the dependent variable will be coded as 0, 1. A 95% two-sided Wald confidence interval for the arm term can then be interpreted in terms of absolute risk and the null hypothesis is rejected if it does not cross the non-inferiority margin. As a sensitivity analysis, a two-sided 95%-Wilson confidence interval for the difference in proportions will be calculated. Only few missing data regarding all relevant endpoints are expected given the rather short period of observation. Nevertheless, conservative imputations will be performed independent of treatment arm. Further sensitivity analyses are planned to adjust for covariates, possibly imbalanced baseline characteristics between groups and/or protocol deviations in multivariable regression models, e.g. for (components of) the primary endpoint and/or in subgroups, which arose from stratification criteria. Furthermore, the odds ratios from logistic regression will be computed to have a relative risk measure in addition to the absolute one, as recommended by statistical guidelines.

Absolute risk differences of major secondary endpoints will be analysed in the same way as the primary endpoint. Kaplan-Meier curves/results of logrank tests will be presented for 28 and 90 days mortality. We expect the time to death to be (nearly) always available. Ventilator-free hours (until 72 h assessment) and SRI and SGRQ at 28 days will be analysed by a linear regression model including randomization arm as factor and stratification criteria as covariates. SRI and SGRQ cannot be determined at baseline due to the patients’ state.

Neither imputation of missing values nor adjustments for multiple testing are planned for secondary/safety endpoints. No interim analysis is planned.

The proportion of patients (with 95% confidence limits) who were randomly allocated to NIV therapy but changed to NHF due to insufficient efficacy and avoid an immediate intubation and vice versa will be analysed. Both the proportion with and without later intubation will be provided. Although these NIV-to-NHF proportions are a form of data exploration, useful estimates on the value of NHF as rescue treatment in patients who do not tolerate NIV may be derived, especially if compared to usually reported proportions of intubation immediately initiated after NIV.

The proportion of switches to another device before intubation will also be compared to investigate potentially existing preferences in favour of NIV.

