## Methods

### Study design

ELVIS is an investigator initiated trial funded by the German Ministry for Education and Research (BMBF KS2018-073). In a legal sense, this trial is regulated by the European Medical Devices Law for use of approved devices in their indication. The legal basis for the study is the German Medical Devices Act (MPG §23b), valid before the MPDG came into force. As such, there is cannot be a legal sponsor. However, Leipzig University is the “Responsible Institution,” and neither the university qua university nor the BMBF played any part in study design. Furthermore, they will play no part in data collection, management, analysis and interpretation of data; writing of the report; and the decision to submit the report for publication. The trial is designed as a prospective, randomized, multi-centre, open label, non-inferiority trial. Blinding is not possible because of the different nature of the two different devices, but the endpoints were chosen to be as objective as possible to avoid potential bias. The analysts will not be blinded. The study will be conducted in about 35 university and community hospitals in Germany involving the pneumology and emergency wards as well as ICU; see supplement for the list of intended sites.

Each trial site receives a study-specific NHF device (through public funds), although other specified devices may also be used. The handling of the devices is carried out according to the manufacturer's instructions. The protocol was approved by the Ethics Committee of all participating centres. The study was registered at ClinicalTrials.gov in May 2021 (NCT04881409). Study monitoring, data handling and organization of the study will be provided by Clinical Trials Centre from the University of Leipzig, Germany.

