### Study endpoints

The primary endpoint is the proportion of patients with treatment failure within 72 h. Treatment failure is defined by (a) switch to another method of non-invasive ventilation or (b) intubation or (c) death.

It is highly recommended that intubation only be initiated if pH < 7.15 and at least one of the following criteria is met: (i) Glasgow Coma Scale (GCS) < 10, (ii) O_2_ saturation < 85% or PaCO_2_ < 45 mmHg despite FiO_2_ > 0.5 and (iii) respiratory rate > 40 cycles/min.

Switching to another method of non-invasive ventilation should only be considered in the following situation:
One of the following criteria is met within 1 h: decrease in pH by at least 0.06, increase in pCO_2_ by at least 10 mmHg, unacceptable decrease in GCS, increase in respiratory rate by at least 20%, insufficient complianceOne of the following criteria is met after 2 h: unacceptable decrease in pH or pCO_2_, clinically unstable compared to last status (beginning at 4 h), insufficient compliance

The most important secondary endpoints are as follows: (a) proportion of patients that fulfil single components of the primary endpoint (i.e. intubation, switch of device or death within 72 h), (b) proportion of patients intubated within 7 days after hospitalization/randomization, (c) overall survival at 28 and 90 days, (d) (invasive) ventilator-free days up to day 28, (e) (invasive) ventilator-free hours until 72 h or until reaching the primary endpoint (whichever comes first), (f) ICU and hospital lengths of stay, (g) proportion of patients requiring sedation and (h) quality of life at day 28 according to St George’s Respiratory Questionnaire (SGRQ) and the Severe Respiratory Insufficiency (SRI) questionnaire, both of which are validated and standard instruments used in patients with obstructive airway diseases [27–29]. Safety issues of interest are device related intolerance/complications and severe diseases acquired under treatment. Compliance and acceptance of devices will also be investigated.

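### The ITT-labelled full analysis set drops patients for pneumonia or SARS-CoV-2 found up to 48 h after randomisation, for a contradictory reason, which can bias the confirmatory risk difference in either direction

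*Protocol article*

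**What the plan says.** All of this is in the protocol article.

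- **Analysis set** (Sample size and statistical analysis). The full analysis set is said to follow the intention-to-treat strategy, but it consists of "all randomized patients with AECOPD and started on ventilatory support".
- **Pneumonia rule** (same section). Pneumonia found within 48 h, which the article labels nosocomial, is given as an example of a reason for removal: "such patients will not be included in the final analysis, since the initial AECOPD diagnosis is found to be erroneous".
- **SARS-CoV-2 rule** (same section). Patients with a positive test within 48 h "will not be included in the full analysis set".
- **Timing.** The allocated device is started immediately after randomisation (Interventions). The primary endpoint is a switch of method, intubation or death within 72 h (Study endpoints).
- **Safety.** The safety issues of interest include "severe diseases acquired under treatment" (Study endpoints).
- **Blinding.** The trial is open label, and "The analysts will not be blinded" (Study design).
- **Confirmatory test.** The two-sided 95% Wald interval for the arm term of a linear regression is compared with a margin of 8 percentage points.

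The article does not say when the 48 h clock starts. I read it as starting at randomisation. If it starts at admission, part of the window may fall before randomisation, but the rule still acts on findings made after it.

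**The concern.** An intention-to-treat set protects the comparison because membership is settled at randomisation. Here it depends on what is found over the next two days, while patients are on the device under test and failures are accruing. Staff who know the allocation make the finding, and analysts who know it build the set.

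The pneumonia rule is the main problem, because its reason does not fit its label. A pneumonia acquired in hospital says nothing about whether the exacerbation diagnosed at admission was real. It could instead be a consequence of treatment, and the article lists severe disease acquired under treatment as a safety issue. A possible harm of a device could therefore remove a patient from the efficacy comparison.

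At stake is the trial's single confirmatory claim. A shift of one or two percentage points matters against a margin of 8.

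**Working it through.** **1. The plan's own figure.** Inputs from Sample size and statistical analysis: 15% failure in both arms, margin 0.08, 80% power, upper limit of a two-sided 95% interval, continuity correction.

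- Uncorrected, per arm: n = 2 × 0.15 × 0.85 × (1.960 + 0.842)² / 0.08² = 312.7.
- Corrected, per arm: (n/4) × [1 + √(1 + 4/(0.08n))]² = 337.3, rounded up to 338, or 676 in total. The article states 680.
- Drop-out: 680/0.95 = 716. The article states 720.

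The sample size reproduces to within rounding. The 5% allowance is described only as drop-out; the 48 h exclusions are not mentioned in it.

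**2. How exclusion acts on the risk difference.** Take the edge of the margin: true failure of 15% on NIV and 23% on NHF, with 360 randomised per arm. Let x be the share of failures removed in an arm and y the share of successes removed.

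- Observed rate: p′ = p(1−x) / [p(1−x) + (1−p)(1−y)]
- Patients left: n′ = 360 × [p(1−x) + (1−p)(1−y)]
- Difference: d = p′(NHF) − p′(NIV), with unpooled SE = √[Σ p′(1−p′)/n′]
- Chance of a false non-inferiority claim: Φ((0.08 − d)/SE − 1.96)

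The article gives no exclusion rates, so every x and y is an assumption.

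| Removed | NIV | NHF | d (points) | SE (points) | False claim |
|---|---|---|---|---|---|
| Nobody | 15.0% | 23.0% | 8.0 | 2.91 | 2.5% |
| 10% of failures and 10% of successes, both arms | 15.0% | 23.0% | 8.0 | 3.07 | 2.5% |
| 10% of failures and 5% of successes, both arms | 14.3% | 22.1% | 7.7 | 2.95 | 3.1% |
| 20% of failures and 10% of successes, both arms | 13.6% | 21.0% | 7.4 | 2.99 | 3.9% |
| 20% of failures and 5% of successes, both arms | 12.9% | 20.1% | 7.2 | 2.87 | 4.8% |
| 20% of failures, no successes, both arms | 12.4% | 19.3% | 6.9 | 2.76 | 5.8% |
| 20% of NHF and 10% of NIV failures, no successes | 13.7% | 19.3% | 5.6 | 2.80 | 13.6% |
| 10% of NHF and 20% of NIV failures, no successes | 12.4% | 21.2% | 8.8 | 2.80 | 1.2% |

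Worked row (20% of failures and 5% of successes, both arms):

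- NIV: 0.15 × 0.8 = 0.120 and 0.85 × 0.95 = 0.8075, so p′ = 0.120/0.9275 = 0.1294 and n′ = 333.9.
- NHF: 0.23 × 0.8 = 0.184 and 0.77 × 0.95 = 0.7315, so p′ = 0.184/0.9155 = 0.2010 and n′ = 329.6.
- d = 0.0716 and SE = 0.0287. Φ(0.0084/0.0287 − 1.96) = Φ(−1.67) = 4.8%.

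**3. How few patients it takes.** Remove NHF failures with no NIV counterpart. Four patients (1.1% of the arm) give (82.8 − 4)/356 − 0.15 = 7.1 points and 4.8%. Eight (2.2%) give (82.8 − 8)/352 − 0.15 = 6.3 points and 8.8%.

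**4. Equal numbers removed do not guarantee safety.** If 5% of each arm is removed and 40% of those removed had failed in both arms, the rates become (0.15 − 0.02)/0.95 = 13.7% and (0.23 − 0.02)/0.95 = 22.1%. The difference is then 8.4 points, biased against NHF. If the failure rates among those removed are 40% and 48%, the difference stays at 8.0. Bias is absent when the exclusions are equally frequent and the excluded patients show the same risk difference as the rest.

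**The case against.** The best defence is intent. Study population requires an exacerbation without other causes of respiratory failure, and the rule is justified as removing patients who never met that. On this view the word nosocomial is a slip, the target is pneumonia already present at admission, and the clash with the safety outcome largely falls away. The article cannot settle this. Even so, detection within 48 h does not separate disease present at baseline from disease acquired afterwards, so the rule would still need rewriting.

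Other points stand and limit the finding:

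- A reader might infer that the rule does bias the result, or always shrinks the difference towards non-inferiority. The article does not support that: the working includes shifts in both directions and cases with none.
- The larger error rates (5.8% and 13.6%) assume that no successful patient is ever excluded. The 13.6% also needs a difference between arms that nothing in the article suggests.
- It is tempting to say that pneumonia is sought mainly in deteriorating patients. The article does not say so; Table 1 schedules optional infection parameters at screening, 24 h and 72 h in both arms alike.
- SARS-CoV-2 positivity is a test result and more plausibly present at baseline, so that rule is weaker.
- The started criterion is weaker too. It refers to ventilatory support, not the allocated device, so a patient who fails to tolerate the device, or who receives the other method, has still started. As support begins at once, non-starters should be few.
- The pneumonia rule is introduced as an example, which in a condensed article does not prove that the list is open. A full list, adjudication rules and further sensitivity sets may be in the full protocol or analysis plan, which are not shown.

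None of this removes the core. The article itself fixes the confirmatory set, and none of the sensitivity analyses it names is described as restoring these patients. Protocol violations are to be discussed with the biometrician before the database is closed, but blinding is not mentioned there.

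**Conclusion.** Wrong as written. The set is labelled intention-to-treat, but membership depends on findings made after randomisation and inside the endpoint window, and the pneumonia rule contradicts its own reason. It can bias the confirmatory risk difference in either direction, by an amount the article does not allow one to estimate. In the scenarios tabulated, the difference at the margin runs from 5.6 to 8.8 points instead of 8.0, and the false non-inferiority rate from 13.6% down to 1.2% instead of 2.5%. All rest on assumed exclusion rates, true failure of 15% and 23%, 360 patients per arm and a normal approximation without covariates. The finding rests mainly on the pneumonia rule; the SARS-CoV-2 and started criteria add the same concern with less force.

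**What to change.** - Make all randomised patients, analysed as allocated, the primary set.
- If exclusions for ineligibility are kept, allow them only where evidence dated before randomisation shows it, from a closed list, decided blind to arm and outcome before the set is locked.
- Delete the word nosocomial or reconcile it with the stated reason.
- Move the present 48 h exclusions to a sensitivity analysis, and report the number and reasons for exclusion by arm.

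The cost is a change of wording in the protocol and analysis plan and one extra analysis; the planned sample size is unchanged. The downside is that a few patients with another diagnosis stay in the primary analysis. The sensitivity analysis shows how much they matter.

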### Study population

Patients are eligible for the study if they suffer from AECOPD in the absence of other causes of respiratory failure. Investigators from the pulmonology or emergency wards or from the intensive care unit will briefly describe the trial and obtain informed consent. A concise consent for is available if treatment has to begin imminently, and the full consent is then required at a later point in time. On the consent form, participants are informed in detail about data handling and storage. This trial does not involve collecting biological specimens for storage.

Specific eligibility criteria are as follows.

*Inclusion criteria*
Acute hypercapnic exacerbation of chronic obstructive pulmonary disease with respiratory acidosis (pH < 7.35)pCO_2_ > 45 mmHgage ≥ 18 yearsWritten informed consent

*Exclusion criteria*
Immediate need for intubationpH < 7.15BMI ≥ 35 kg/m^2^Established home-NIV or home-CPAPEnd-stage disease with DNI/DNR orderDiseases that could influence the primary endpoint: e.g. acute heart infarction, cardiogenic lung oedema, acute and massive lung embolism (hypertensive), chronic dialysis with metabolic acidosis, unstable rib fracture influencing ventilation, injury to the face prohibiting use of a face maskAcute disease that precludes participation in the trialTracheotomized patientsPsychological/mental or other inabilities to supply required informed consentParticipation in other interventional trialsSuspected lack of compliance

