### Randomization, recruitment and data collection

Randomization will be performed centrally, via a secure web-based tool. The allocation to the intervention arm (randomization ratio 1:1) uses a minimization procedure with a stochastic component that takes into account trial centre, pH ≤/> 7.3 and BMI ≤/> 30 kg/m^2^. The randomization result forwarded automatically via email to the investigator and the Clinical Trial Centre Leipzig.

Adequate recruitment will be encouraged through regular Newsletters including current recruitment status, regular consultations with trial sites by the monitor/coordinating investigator and trial meetings.

The schedule of study visits and list of parameters collected can be found in Table 1. Within the first 24 h, data are collected at 1, 2, 4, 6, 12 and 24 h after which collection takes place at 36, 48 and 72 h. There is a discharge visit and one at day 7 as well as telephone visits on days 28 and 90.

**Table 1 Tab1:** Schedule for study interventions according to Recommendations for Interventional Trials (SPIRIT) indications

Examination/assessment		Treatment											Follow-up		
	Screening	Visit 0	Visit 1						Visit 2		Visit 3		Visit 4	Visit 5^**a**^	Visit 6^**a**^
Timepoint		0 h	1 h ± 30 min	2 h ± 30 min	4 h ± 30 min	6 h ± 30 min	12 h ± 60 min	24 h ± 60 min	36 h ± 90 min	48 h ± 120 min	72 h ± 180 min	discharge	day 7^**b**^ ± 1 day	day 28	day 90
Informed consent	X^c^											X^d^			
Inclusion criteria/exclusion criteria	X														
Randomization		X													
Patient characteristics (anamnesis, comorbidity)	X														
Medication	X							X^e^		X^e^	X^e^	X			
Clinical parameters (heart rate, respiratory rate, blood pressure, Borg’s scale)	X		X	X	X	X	X	X	X	X	X	X	X		
Adverse events/side-effects			X	X	X	X	X	X	X	X	X	X	X	X	X
Glasgow coma scale (GCS)	X		X	X	X	X	X	X	X	X	X	X			
Blood gas analysis (BGA): pO_2_, pCO_2_, pH, SpO_2_, FIO_2_	X		X	X	X	X	X	X	X	X	X	X	X		
Therapy according to allocated device: device parameters		X	X^6^	X	X	X	X	X	X	X	X	X	X^g^	X^f^	X^f^
Therapy: oxygen supplement		X	X	X	X	X	X	X	X	X	X	X	X^f^	X^f^	X^f^
infection parameters and biomarkers (optional)	X							X^e^			X^e^				

^a^Visits 5 and 6 are conducted by telephone

^b^Assessment of intubation; not applicable, if patient is already discharged since no intubation can be stated in this care

^c^Standard (long) version of informed consent OR concise (short) version of informed consent

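### The confirmatory model uses pH and BMI only as two-level factors and omits baseline pCO2; adding all three as prespecified continuous covariates would be a modest, optional gain in precision

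*Protocol article*

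**What the plan says.** All references are to the protocol article.

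- **Confirmatory model** (Sample size and statistical analysis): the outcome is coded 0/1 and "linear regression with the stratification variables and the arm as covariates will be used". The two-sided 95% Wald interval for the arm term is read as an absolute risk difference and compared with the 8-point margin.
- **Stratification variables** (Randomization, recruitment and data collection): the minimisation "takes into account trial centre, pH ≤/> 7.3 and BMI ≤/> 30 kg/m^2". The analysis section does not restate the coding. As defined, pH and BMI are two-level factors, and centre is the third variable.
- **Baseline data:** Table 1 schedules "Blood gas analysis (BGA): pO_2_, pCO_2_, pH, SpO_2_, FIO_2" at screening. Under Study population, entry requires "respiratory acidosis (pH < 7.35" and pCO2 above 45 mmHg, and excludes pH below 7.15 and BMI of 35 or more. Exact pH, pCO2 and BMI should therefore exist for essentially every randomized patient.
- **Other adjustment** (Sample size and statistical analysis): "Further sensitivity analyses are planned to adjust for covariates, possibly imbalanced baseline characteristics between groups", among other things. These analyses are separate from the confirmatory one.
- **Sample size** (same section): calculated by "assuming that treatment failure is 15% in both arms", with a continuity-corrected Z-test and no covariates.

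**The concern.** Splitting a prognostic variable at one point treats all patients on the same side as alike. Eligible pH runs from 7.15 to just under 7.35, so the lower stratum pools 7.16 with 7.30. The article itself suggests that baseline gases bear on the outcome. pH is a minimisation factor, the intubation recommendation is framed around a pH threshold, and changes in pH and pCO2 are listed among the grounds for switching device. Intubation and switching are both components of the primary endpoint. Yet pCO2 is not in the confirmatory model.

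What is at stake is precision. In a linear model, prognostic covariates reduce the residual variance and narrow the interval for the arm term, which is the interval held against the 8-point margin. Using values already collected would do this without changing the estimand.

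**Working it through.** **Step 1: reproduce the plan's figure without covariates.** Inputs from the sample size section: p = 0.15 in both arms, margin 0.08, two-sided 95% interval (one-sided 0.025), power 80%, 1:1 allocation.

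- Uncorrected n per arm = 2p(1−p)(1.960 + 0.842)²/0.08² = 312.7, so 313 per arm and 626 in total.
- With the continuity correction, n′ = (n/4)·[1 + √(1 + 4/(0.08n))]² = 337.3, so 338 per arm and 676 in total. The article states 680, a close match.
- At 340 per arm, SE = √(2 × 0.15 × 0.85/340) = 0.02739. Corrected power = Φ((0.08 − 1/340)/SE − 1.960) = 80.3%. Without the correction it is 83.2%. The 95% half-width is 1.960 × SE = 5.37 points.
- Dropout: 680/0.95 = 716 and 720 × 0.95 = 684, both consistent with recruiting 720.

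The planned power therefore does not rely on covariate adjustment.

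**Step 2: what any extra explained variance is worth.** If covariates explain a share R² of the outcome variance, the variance of the arm term is multiplied by (1 − R²). At 340 per arm, with the continuity correction:

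| Extra R² | Total N for 80% power | Power at 680 | Half-width (points) |
|---|---|---|---|
| 0 | 676 | 80.3% | 5.37 |
| 1% | 670 | 80.7% | 5.34 |
| 2% | 664 | 81.1% | 5.31 |
| 5% | 644 | 82.3% | 5.23 |
| 10% | 612 | 84.3% | 5.09 |

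**Step 3: cut versus continuous covariates.** The documents give no prognostic strength, so this step is a simulation under assumptions: pH normal (7.28, SD 0.05) truncated to 7.15–7.35; BMI normal (26, SD 5) truncated to 15–35; pH–pCO2 correlation −0.5; failure rate 15%; log-odds linear in each covariate; centre left out of both models. R² is from a linear fit to the 0/1 outcome. Patients gained = 680 × [1 − (1 − R² continuous)/(1 − R² cut)].

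| Assumed odds ratio per SD (lower pH / higher pCO2 / higher BMI) | R², cut pH + BMI | R², continuous pH + pCO2 + BMI | Power, cut → continuous | Patients gained of 680 |
|---|---|---|---|---|
| Weak: 1.2 / 1.1 / 1.1 | 0.4% | 0.9% | 80.5% → 80.7% | about 4 |
| Moderate: 1.5 / 1.2 / 1.2 | 1.6% | 3.9% | 81.0% → 81.9% | about 16 |
| Strong: 2.0 / 1.5 / 1.5 | 4.0% | 11.7% | 81.9% → 85.0% | about 55 |
| Very strong: 2.5 / 1.5 / 2.0 | 6.3% | 16.7% | 82.8% → 86.9% | about 75 |

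Worked example, moderate row: (1 − 0.0394)/(1 − 0.0160) = 0.976, and 680 × (1 − 0.976) is about 16. The half-width goes from 5.37 × √0.984 = 5.33 to 5.37 × √0.9606 = 5.26 points.

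The table replaces the cut terms with continuous ones. The suggested fix keeps both, which cannot lower R².

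**The case against.** The strongest reply is that nothing here is broken. The covariate set is fixed in advance, the arm term is the intended risk difference, and the stated size and power reproduce without covariates, so any gain from adjustment is a bonus. All of that stands. It also stands that the gain rests on assumed effects. Eligibility narrows the pH range, and the composite counts switches for insufficient compliance, which need not follow baseline acidosis. The simulation's linear log-odds also favours continuous coding. Weak effects, worth a fraction of a power point, are quite possible.

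A second reply is that the protocol is final and recruiting, so changing the primary model may need a formal amendment. Because the analysts are unblinded, a late choice of covariates could itself damage credibility. This is a condition on timing rather than a reason against the change: it is met if the terms are fixed without reference to outcome data by arm.

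Three stronger readings might be inferred, and the documents do not support them:

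- **That the model adjusts for pH and BMI alone.** Trial centre is also a stratification variable and so is in the model.
- **That adjusting for the cut factors brings no benefit.** It matches the analysis to the minimisation, avoids an overstated standard error and fixes a small covariate set in advance.
- **That covariates will be chosen by observed imbalance.** The phrase "possibly imbalanced baseline characteristics between groups" concerns sensitivity analyses only. Covariates are listed there as a separate item, and the exact list is normally left to the SAP, which is not shown.

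**Conclusion.** The planned confirmatory analysis is valid, prespecified and consistent with its sample size. It is less efficient than it could be, because it uses pH and BMI only as two-level factors and leaves out pCO2 when exact values of all three should be available. At the assumed 15% failure rate the gain from continuous terms is about 0.2 to 1 point of power (about 4 to 16 of 680 patients) if the covariates are weak to moderate predictors, and about 3 points (about 55 patients) if they are strong. These sizes depend on prognostic strengths and covariate distributions that the documents do not give. This is an optional efficiency improvement of modest priority. It is not evidence of bias, inadequate planned power or a contradiction.

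**What to change.** In the confirmatory linear model, keep trial centre and the two minimisation factors, and add screening pH, pCO2 and BMI as continuous covariates. Name them in the SAP or an amendment before anyone examines outcome data by arm. The arm coefficient and its Wald interval are still read as the absolute risk difference against the 8-point margin.

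The cost is three degrees of freedom among about 680 patients, about one sentence of text, and a documented change to the plan. The section on protocol modifications requires a formal amendment if the change is judged substantial. No new data are needed, and missing values should be rare because all three are needed to establish eligibility.

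### For death within 72 h the main interval is the linear-regression Wald interval; if deaths are rare, its upper limit understates a true excess on NHF more often than the nominal 2.5%

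*Protocol article*

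**What the plan says.** All of this is in the protocol article, under Study endpoints and under Sample size and statistical analysis.

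- Primary analysis: "linear regression with the stratification variables and the arm as covariates will be used", and "A 95% two-sided Wald confidence interval for the arm term can then be interpreted in terms of absolute risk".
- Sensitivity analysis of the primary endpoint: "As a sensitivity analysis, a two-sided 95%-Wilson confidence interval for the difference in proportions will be calculated".
- Secondary endpoints: "Absolute risk differences of major secondary endpoints will be analysed in the same way as the primary endpoint". This is the sentence at issue.
- First in the list of most important secondary endpoints is the "proportion of patients that fulfil single components of the primary endpoint (i.e. intubation, switch of device or death within 72 h").

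Read together, these make the Wald interval the main interval for 72 h death, with the Wilson interval at most a sensitivity analysis. No margin is set for 72 h death, and no multiplicity adjustment is planned for secondary endpoints. The article gives no expected 72 h death rate. Its only mortality figure, 183 per 1000 in the Background, has no 72 h time frame.

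**The concern.** The Wald interval takes its standard error from the observed proportions. When the NHF arm by chance has few deaths, the estimated difference and the standard error are both too small, so the upper limit is low for two reasons at once. At proportions near 15% this hardly matters. With a handful of deaths per arm it does, and with no deaths in either arm the interval has zero width.

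The side affected is the one a reader of a non-inferiority result will look at: how large an excess of deaths on NHF is still compatible with the data. The Discussion describes the comparator as reducing mortality, so the question will be asked whatever the primary result.

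**Working it through.** **Inputs.** From Sample size and statistical analysis: "680 patients need to be analysed to have 80% power", so 340 per arm; "assuming that treatment failure is 15% in both arms"; margin 8 points; two-sided 95% intervals. Assumed, because not given: NIV risk of death within 72 h between 0.25% and 4%.

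**The plan's own figure.** Without continuity correction, n per arm = (1.96 + 0.8416)² × 2 × 0.15 × 0.85 / 0.08² = 312.7. With it, n = (312.7/4) × [1 + √(1 + 4/(312.7 × 0.08))]² = 337.3, rounded up to 338, or 676 in total. That agrees with 680. Exact power of the continuity-corrected pooled Z-test at 340 per arm is 80.3%.

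**Intervals compared.** Let p1 be the observed proportion on NHF, p2 that on NIV, and n = 340.

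- Wald: (p1 − p2) ± 1.96 × √[p1(1 − p1)/n + p2(1 − p2)/n]. With equal arms, the unadjusted linear-regression interval is almost identical.
- Wilson-based upper limit: (p1 − p2) + √[(u1 − p1)² + (p2 − l2)²], where l and u are the single-arm Wilson limits. The lower limit is the mirror image. The article does not say which Wilson form it means, so this one (Newcombe's) is an assumption.

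**Upper-limit miss rate.** Sum Bin(x1; 340, π1) × Bin(x2; 340, π2) over all pairs of counts whose upper limit lies below π1 − π2, where π1 and π2 are the true risks. The nominal value is 2.5%.

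| True risk, NIV v NHF | Wald upper miss | Wilson-based upper miss | Wald two-sided coverage |
|---|---|---|---|
| 0.25% v 1.25% | 8.07% | 1.15% | 91.4% |
| 0.5% v 1.5% | 5.64% | 1.48% | 93.5% |
| 0.5% v 2% | 5.03% | 1.55% | 93.8% |
| 1% v 2% | 3.55% | 1.80% | 95.0% |
| 1% v 3% | 3.99% | 2.14% | 94.6% |
| 1% v 4% | 4.22% | 2.14% | 94.1% |
| 2% v 4% | 3.20% | 2.23% | 94.9% |
| 3% v 5% | 2.88% | 2.31% | 95.0% |
| 4% v 6% | 2.68% | 2.33% | 95.0% |
| 15% v 23% (primary, at the margin) | 2.51% | 2.55% | 95.0% |

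At an NIV risk of 3% the Wald rate stays below 3% for excesses up to 4 points and is 3.1% at 5 points. With equal risks between 0.5% and 4% it is 1.7% to 2.6%.

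**With covariates.** Simulating the linear model with 35 centres and the pH and BMI strata (20,000 runs) gave 5.1% at 0.5% v 2%, 3.8% at 1% v 3%, 4.2% at 1% v 4% and 2.6% at 15% v 23%. A robust standard error gave the same rates, so neither adjustment nor a sandwich variance removes the effect.

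**Two concrete cases.**

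- NIV 0, NHF 4 deaths: difference 4/340 = 1.18 points, standard error √(0.01176 × 0.98824/340) = 0.585 points, Wald interval 0.03 to 2.32. The Wilson limits for 4/340 are 0.46% and 2.99%, and the upper limit for 0/340 is 1.12%. The Wilson-based interval is therefore 1.18 − √(0.72² + 1.12²) = −0.15 to 2.99.
- No deaths in either arm: the Wald interval is 0 to 0, the Wilson-based interval ±1.12 points. At a true risk of 0.5% in both arms this has probability 0.995^680 = 3.3%.

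**The case against.** **The rarity is assumed.** This stands. No 72 h rate is given, and the size of the effect depends on it. A reader might infer that the upper limit errs about twice as often as it should in general. The documents do not support that: twice fits an NIV risk near 0.5%, while the ratio is about 1.3 at 2% v 4%, about 1.15 at 3% v 5% and over 3 at 0.25% v 1.25%.

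**The Wilson interval may already be covered.** Analysis in the same way as the primary endpoint can be read to include its sensitivity analysis. The text does not settle this. On that reading the Wilson interval would still stand behind the Wald interval, and the point becomes which of the two is the reported one.

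**This is SAP detail.** Partly so. An SAP that is not shown may already name another interval, which would close the point. But the article does not leave the choice open; it assigns a method to these endpoints.

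**No decision depends on it.** This also stands. There is no margin or decision rule for 72 h death, two-sided coverage is close to nominal from an NIV risk of 1% upwards, and survival at 28 and 90 days is analysed by Kaplan-Meier and log-rank. The average upper limits are not far apart: 4.08 v 4.47 points at 1% v 3%, and 4.55 v 4.83 at 2% v 4%.

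**False signals.** The 0 v 4 case, where the Wald interval excludes zero and Fisher's test gives p = 0.12, invites the inference that the plan will produce too many false differences in mortality. It does not show that. At equal risks of 0.5% the lower limit errs in only 1.7% of trials, and Fisher's test is itself conservative.

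**Conclusion.** The point holds as a minor one. The protocol makes the linear-regression Wald interval the main interval for death within 72 h. If deaths are rare and there is a true excess on NHF, the upper limit lies below that excess more often than 2.5%: 5.0% to 5.6% at an NIV risk of 0.5% and 3.6% to 4.0% at 1%, for excesses of 1 to 2 points, and 3.2% at 2% v 4%. The problem nearly disappears at 3% and above. The Wilson-based interval stays below 2.5% in every rare-event setting examined.

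This rests on 340 analysed patients per arm and on assumed 72 h death rates. It is an imbalance on one side, not a general failure of coverage. The primary analysis is sound (2.5% at 15% v 23%), and nothing here inflates the type I error of the non-inferiority claim.

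**What to change.** Add one sentence to the SAP: for death within 72 h, the reported interval is the two-sided 95% Wilson-based interval for the difference in proportions, with its form named, and the adjusted linear-regression Wald interval is supportive. Fix this by endpoint in advance. A switch triggered by the observed number of events would make the reported method depend on the data and would need a threshold that has no basis in the documents. Leave the confirmatory analysis of the primary endpoint as it is.

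The cost is a slightly wider interval (upper limit on average about 0.3 to 0.4 points higher in the 2% v 4% and 1% v 3% settings) that is not adjusted for the stratification variables. Sample size, data collection and the primary test do not change.
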